## 15.4 Assessment of Severity

The PI or designee should make an assessment of severity for each AE according to the following categories:

| Category                      | Definition                                                                                                                              |
|-------------------------------|-----------------------------------------------------------------------------------------------------------------------------------------|
| Mild
(Grade 1)             | A reaction that is easily tolerated by the trial participant, causing minimal discomfort and not interfering with every day activities. |
| Moderate
(Grade 2)         | A reaction that is sufficiently discomforting to interfere with normal everyday activities.                                             |
| Severe
(Grade 3)           | A reaction that prevents normal everyday activities.                                                                                    |
| Life Threatening
(Grade 4) | A reaction that has life threatening consequences; urgent intervention indicated.                                                       |
| Death
(Grade 5)            | A reaction that results in death.                                                                                                       |

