### Inclusion criteria

1. Moderate to severe ARDS as defined by the Berlin definition (62).
  - a) Onset within 1 week of identified insult
  - b) Within the same 24-hour time period
    - i. Hypoxic respiratory failure ( $\text{PaO}_2/\text{FiO}_2$  ratio  $\leq 27\text{kPa}$  on  $\text{PEEP} \geq 5\text{ cmH}_2\text{O}$ )
    - ii. Bilateral infiltrates on chest X-ray consistent with pulmonary oedema not explained by another pulmonary pathology
    - iii. Respiratory failure not fully explained by cardiac failure or fluid overloadThe time of onset of ARDS is when the last ARDS criterion is met.
2. Patient is receiving invasive mechanical ventilation.
3. COVID-19 based on clinical diagnosis or PCR test or other cause of ARDS.

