### **9.2 Informed Consent Procedure**

The study will be conducted in accordance with the ethical principles that have their origin in the Declaration of Helsinki. The Principal Investigator (PI) (or designee) is responsible for ensuring that informed consent for trial participation is given by each patient or a legal representative. An appropriately trained doctor or nurse may take consent. The person taking informed consent must be GCP trained, suitably qualified and experienced and have been delegated this duty on the delegation log. Appropriate signatures and dates must be obtained on the informed consent documentation prior to collection of trial data and administration of the trial drug. If no consent is given a patient cannot be enrolled into the trial.

The incapacitating nature of the condition precludes obtaining prospective informed consent from participants. In this situation informed consent will be sought from a Personal Legal Representative (Per LR) or Professional Legal Representative ([name]).

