### 15.8 Adverse Event Reporting

As REALIST is recruiting in a population that is already in a life-threatening situation, it is expected that many of the patients will experience AEs. Events that are expected in this population (i.e. events in keeping with the underlying condition) should not be reported as AEs.

Examples of such adverse events include transient hypoxemia, agitation, delirium, organ failure, nosocomial infections, skin breakdown, and gastrointestinal bleeding. Such events will not be considered reportable adverse events unless the event is considered by the investigator to be associated with the study drug, or unexpectedly severe or frequent for an individual patient with ARDS.

The following pre-specified adverse events occurring within 6 hours of the start of infusion will be collected:

1. An increase in vasopressor dose greater than or equal to the following:
  - a. Norepinephrine: 0.1 mcg/kg/min
  - b. Epinephrine: 0.1 mcg/kg/min
  - c. Commencement of any vasopressor including norepinephrine, epinephrine, vasopressin, phenylephrine, and dopamine
2. New ventricular tachycardia, ventricular fibrillation or asystole
3. New cardiac arrhythmia requiring cardioversion
4. Hypoxemia requiring an increase in FiO2 of 0.2 or more and an increase in PEEP of 5 or more to maintain SpO2 in the target range
5. Clinical scenario consistent with transfusion incompatibility or transfusion-related infection (e.g. urticaria, new bronchospasm).

The following pre-specified adverse events occurring within 24 hours of the start of infusion will be collected:

1. Any death.
2. Any cardiac arrest.
3. Temperatures recorded as >38.5°C or temperatures that are recorded as >38.5°C prior to study drug administration and have increased by ≥1°C.

The investigator should attempt, if possible, to establish a diagnosis based on the subject's signs and symptoms. When a diagnosis for the reported signs or symptoms is known, the investigator should report the diagnosis as the AE, rather than reporting the individual symptoms.

The investigator should follow all AEs observed during the study until they are resolved or stabilised, or the events are otherwise explained.

All AEs should be treated appropriately. The action taken to treat the AE and the outcome will be recorded in the CRF.

All AEs, ARs and UARs should be reported on the AE Form within the CRF.

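### Severity Grades 1 to 3 cannot be applied to adverse events while participants are ventilated and incapacitated, so the grade recorded in that period is arbitrary

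*Protocol*

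**What the plan says.** Section 15.4 of the protocol makes grading compulsory: "The PI or designee should make an assessment of severity for each AE according to the following categories". Section 15.2 likewise lists severity among the assessments due for all AEs. The first four categories in section 15.4 are:

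- Grade 1: "A reaction that is easily tolerated by the trial participant, causing minimal discomfort and not interfering with every day activities"
- Grade 2: "A reaction that is sufficiently discomforting to interfere with normal everyday activities"
- Grade 3: "A reaction that prevents normal everyday activities"
- Grade 4: "A reaction that has life threatening consequences; urgent intervention indicated"

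Grade 5 is death.

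The population is set by an inclusion criterion in section 8.3, "Patient is receiving invasive mechanical ventilation", and described in section 9.2: "The incapacitating nature of the condition precludes obtaining prospective informed consent from participants".

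Section 15.8 exempts events typical of critical illness from AE reporting. The exemption is lifted if the investigator links the event to the study drug, or finds it "or unexpectedly severe or frequent for an individual patient with ARDS".

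**The concern.** A severity scale is useful only if two observers who see the same event would tend to choose the same grade. Here the lower three grades rest on things that a ventilated, incapacitated patient does not have or cannot convey. Sites would have to improvise, and the protocol gives them no alternative anchor.

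Section 7 states that safety is the main focus of phase 2, and section 15.8 brings AE records into the safety analysis. If the grade depends on who filled in the form, a description of events by severity tells the reader little about the product, and it would be hard to repair afterwards.

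**Working it through.** The protocol gives no figure on this point and no arithmetic applies. The check sets the definitions against the population and then traces where the grade is used.

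**Step 1: can each grade be assigned in a ventilated, incapacitated participant?**

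| Grade | What separates it from its neighbours | Can it be judged? |
|---|---|---|
| 1 | Tolerance, minimal discomfort, activities unaffected | No: discomfort usually cannot be reported, and there are no activities to affect |
| 2 | Discomfort that interferes with activities | No, for the same reasons |
| 3 | Activities prevented | No: activities are already absent before the event |
| 4 | Threat to life, urgent intervention | Yes |
| 5 | Death | Yes |

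Section 12.3 adds that, for bronchoscopy, sedation and analgesia are given as standard care to prevent discomfort. That weakens discomfort further as a marker.

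**Step 2: what does a rater do?** Take a non-life-threatening event in ICU. Read one way, it interferes with nothing further and is Grade 1. Read the other way, activities are prevented and it is Grade 3. The text does not settle the choice, and no other section supplies a criterion.

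**Step 3: when does this apply?** From entry until the participant recovers enough for the anchors to mean something. Table 1 asks for the study drug ideally within 12 hours of enrolment, so the infusion falls in this period. Section 15.7 runs AE reporting to 90 days after dosing, so the anchors become usable for later events in those who recover.

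**Step 4: what depends on Grades 1 to 3?**

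- Primary safety outcome (section 7.1): the incidence of serious adverse events, which rests on the separate seriousness criteria in section 15.5. Not dependent.
- Phase 1 dose limiting toxicity (section 15.8): any serious adverse reaction, so seriousness and causality. Not dependent.
- SUSAR status: Table 3 mentions severity when it defines an unexpected reaction, but section 15.6 declares every adverse reaction unexpected. Not dependent.
- Pre-specified infusion events at 6 and 24 hours (section 15.8): collected whatever their grade, largely on explicit criteria such as vasopressor dose, FiO2 with PEEP, and temperature. Not dependent.
- Reporting of ICU-typical events (section 15.8): three alternative triggers, namely association with study drug, unexpected severity and unexpected frequency. None cites a grade from section 15.4.
- Severity recorded with each AE, as part of the descriptive safety data (sections 14.3 and 15.8). Dependent.

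**The case against.** The strongest reply has four parts.

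First, Grade 3 speaks of a reaction that does the preventing. Incapacity caused by ARDS or sedation is not caused by the event, so it does not follow that every non-life-threatening event is Grade 3. This is right, and it rules out saying that all events pile up in one grade. It does not rescue the scale, because on that reading Grade 1 becomes equally arguable.

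Second, a reader might infer that the faulty grades decide whether organ failure, infection or bleeding is reported at all, and so distort the count of serious adverse events. The protocol does not support this. Severity is one of three triggers in section 15.8. It is judged against what is usual in ARDS, which is already a yardstick suited to ICU, and the rule is not tied to the grades. What stands is narrower: section 15.8 does not say how unexpected severity is to be judged in practice or how it relates to section 15.4.

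Third, the measures that matter most for safety do not use the grade, and section 14.3 plans only a descriptive AE analysis without promising a table by severity. This stands and limits the weight of the point.

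Fourth, changing the scale after phase 1 is complete reduces comparability, since section 14.3 reports phase 2 AEs in the same way as phase 1. This is a real cost. However, the phase 1 grades were to be assigned under the same unusable anchors, so little of value is lost.

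**Conclusion.** The point holds as a measurement defect of limited reach. A compulsory scale does not fit the patients it must grade: three of its five categories cannot be told apart while the patient is ventilated and incapacitated, which includes the infusion. Recorded severity below Grade 4 is arbitrary in that period.

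A reader might also infer that the defect covers most of the first 14 days, or that it reaches expectedness through Table 3. The protocol gives no duration of ventilation, and section 7.1 names extubation as a competing effect in its choice of day 7, so the first has no source. Section 15.6 removes the second.

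The conclusion assumes that participants remain ventilated from enrolment to infusion, and that ventilated patients generally cannot report discomfort. Both fit the protocol's own description of the population. The change is a cheap improvement. The safety endpoints stand without it.

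**What to change.** In section 15.4, for events while the patient is ventilated or in ICU, define the lower grades by what staff can observe:

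- Grade 1: no intervention and no change in support.
- Grade 2: minor or non-urgent intervention, without new organ support.
- Grade 3: new or clearly increased organ support, or an invasive intervention, not immediately life-threatening.

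Keep Grades 4 and 5 as they are, and keep the present wording of Grades 1 to 3 for events after ICU discharge. Section 12.2 already collects the date and time of critical care discharge, so the switch point is on record. Do not use a longer ICU stay as a Grade 3 criterion: it would duplicate the seriousness criterion on prolonged hospitalisation in section 15.5 and blur severity with seriousness.

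In section 15.8, state that unexpected severity is judged against the expected course of ARDS, and how that judgement relates to the grades in section 15.4. Changing the table alone would leave this open.

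Cost: one table, one sentence, CRF help text and site training, with no new data items. A protocol amendment may be needed, with approvals under section 17.4 if it is substantial. Grades would be less directly comparable with the completed phase 1, and grades before and after ICU discharge would rest on different anchors, so reports should say which anchors applied.

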### 15.5 Assessment of Seriousness

The PI or designee should make an assessment of seriousness i.e. is this is an adverse event, adverse reaction or suspected unexpected adverse reaction that:

- Resulted in death.
- Is life-threatening.
- Requires hospitalisation or prolongation of existing hospitalisation.
- Results in persistent or significant disability or incapacity.
- Consists of a congenital anomaly or birth defect.
- Is any other important medical event(s) that carries a real, not hypothetical, risk of one of the outcomes above.

### 15.6 Assessment of Expectedness

The PI or designee is required to make an assessment of expectedness if the event is possibly, probably or definitely related to the study drug. Although MSCs have previously been administered to patients with ARDS (48) as this specific MSC product has not been administered to patients with ARDS before, there are no expected events and all ARs will be considered unexpected. Therefore all SARs will be considered as SUSARs.

### 15.7 Adverse Event Reporting Period

The AE reporting period for the trial begins upon the signature of informed consent and ends 90 days following the last administration of the study drug.

All AEs and SAEs that occur during this time will be followed until they are resolved or are clearly determined to be due to a patient's stable or chronic condition or intercurrent illness(es).

### 15.8 Adverse Event Reporting

As REALIST is recruiting in a population that is already in a life-threatening situation, it is expected that many of the patients will experience AEs. Events that are expected in this population (i.e. events in keeping with the underlying condition) should not be reported as AEs.

Examples of such adverse events include transient hypoxemia, agitation, delirium, organ failure, nosocomial infections, skin breakdown, and gastrointestinal bleeding. Such events will not be considered reportable adverse events unless the event is considered by the investigator to be associated with the study drug, or unexpectedly severe or frequent for an individual patient with ARDS.

The following pre-specified adverse events occurring within 6 hours of the start of infusion will be collected:

1. An increase in vasopressor dose greater than or equal to the following:
  - a. Norepinephrine: 0.1 mcg/kg/min
  - b. Epinephrine: 0.1 mcg/kg/min
  - c. Commencement of any vasopressor including norepinephrine, epinephrine, vasopressin, phenylephrine, and dopamine
2. New ventricular tachycardia, ventricular fibrillation or asystole
3. New cardiac arrhythmia requiring cardioversion
4. Hypoxemia requiring an increase in FiO2 of 0.2 or more and an increase in PEEP of 5 or more to maintain SpO2 in the target range
5. Clinical scenario consistent with transfusion incompatibility or transfusion-related infection (e.g. urticaria, new bronchospasm).

The following pre-specified adverse events occurring within 24 hours of the start of infusion will be collected:

1. Any death.
2. Any cardiac arrest.
3. Temperatures recorded as >38.5°C or temperatures that are recorded as >38.5°C prior to study drug administration and have increased by ≥1°C.

The investigator should attempt, if possible, to establish a diagnosis based on the subject's signs and symptoms. When a diagnosis for the reported signs or symptoms is known, the investigator should report the diagnosis as the AE, rather than reporting the individual symptoms.

The investigator should follow all AEs observed during the study until they are resolved or stabilised, or the events are otherwise explained.

All AEs should be treated appropriately. The action taken to treat the AE and the outcome will be recorded in the CRF.

All AEs, ARs and UARs should be reported on the AE Form within the CRF.

These events will be included as part of the safety analysis for the trial and do not require expedited reporting to the CTU.

Any SAE considered at least possibly related to the study drug will be reported by the investigators whenever they become aware of it. An SAE will be defined as related to the IMP (ie a SAR) if assessed as being possibly, probably or definitely related to the IMP.

All SAEs, SARs and SUSARs should be reported using the SAE Reporting Form and must be reported to the CTU within 24 hours of becoming aware of the event to [[contact]](mailto:[contact]). All SAEs, SARS and SUSARs should also be reported on the AE Form within the CRF.

The CTU is responsible for reporting SAEs to the Sponsor, REC and MHRA within the required timelines as per the regulatory requirements. A fatal or life threatening SUSAR must be reported within 7 days after the CTU has first knowledge of such an event. Relevant follow up

information will be sought and communicated within an additional 8 days. All other SUSARs will be reported to MHRA and REC within 15 days after the knowledge of such an event.

Dose limiting toxicity in the phase 1 trial will be defined as any SAR.

Trial specific guidelines will provide details of the communication plan to provide the study team at each site with information on serious adverse events occurring during the course of the trial.

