#### 4.6 Dose regimen rationale

The dose range for the Phase 1 study and the choice of a single infusion were based on available pre-clinical data. In a rodent model of E. coli induced ARDS (34) a dose-range was studied (2, 5, 10 million cells/kg). Efficacy, as determined by arterial oxygenation, inflammatory cytokine reduction and bacterial clearance was demonstrated at 5 and 10 million cells/kg.

In a clinically relevant ovine model of ARDS induced by smoke inhalation and *Pseudomonas aeruginosa*, sheep were randomised to receive one of two doses of human bone marrow-derived plastic adherent MSCs (5 or  $10 \times 10^6$  cells/kg) reconstituted in Plasma-Lyte or identical Plasma-Lyte A control 1 hour following injury. A single dose of intravenous MSCs caused a significant 3-fold improvement in oxygenation without adverse haemodynamic or respiratory events. The P/F ratio was similar in groups treated with 5 or  $10 \times 10^6$  cells/kg (44). In a pig animal model of oleic acid induced lung injury, infusion of  $2 \times 10^6$  cells/kg reduced lung tissue nuclear NFkB translocation (50).

In the phase 1 START trial in patients with moderate to severe ARDS a dose-range of 1, 5 and 10 million cells/kg was studied. Although a small study, there was no significant difference in terms of efficacy between the doses in surrogate clinical outcomes [43]. In a human study of diabetic nephropathy, 150 but not 300 million MSCs improved renal function (51). Similarly in a study of patients with degenerative spinal disc disease, a single injection of 6million MSCs was more efficacious than 18million cells (52).

There are theoretical concerns that at very high doses coagulation markers on the MSC surface may be triggered, leading to loss of cells and activation of coagulation system in recipients. These effects have not been identified in patients treated with the dose range  $1-3 \times 10^6$  cells/kg (53).

We have chosen to initially assess the safety of Orbccl-C over a dose-range of 1-6 million cells/kg, a dose range compatible with most previous human clinical trials of MSCs. To simplify cell manufacture and delivery of the intervention we have chosen 100, 200 and 400 million cells which equates range of approx. 1.4, 2.8 and 5.7 million cells/kg for predicted body weight of 70kg.

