| 
Reactions to Cryopreservatives (e.g. DMSO)
 
DMSO is added to all MSC products being cryopreserved to protect the MSC from hypothermal damage. The infusion of DMSO has side effects and consequences that study personnel need to be aware of
 | 
 
• metallic/garlic taste
 
• nausea/vomiting
 
• flushing of face
 
• intestinal cramps
 
• acute hypertension
 
• bradycardia (first, second, or third degree atrioventricular block on electrocardiogram)
 
 | 
 
• Pause MSC infusion.
 
• Check vital signs and O2 saturation.
 
• Administer additional anti-emetics if appropriate.
 
• If bradycardia, perform an electrocardiogram. If associated with hypotension, stop infusion and administer atropine 0.5-1mg.
 
• If bradycardia is present and ECG shows third degree atrio-ventricular block, consider placement of a temporary pacemaker. Consult Cardiology.
 
• Resume MSC infusion after reasonable resolution of signs and symptoms if considered safe to do so.
 
 |

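### The pre-specified infusion events in section 15.8 leave out the bradycardia, AV block and hypertension that Appendix 3 names as cryopreservative reactions

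*Protocol*

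**What the plan says.** Protocol section 15.8 sets two short lists. The first opens with "The following pre-specified adverse events occurring within 6 hours of the start of infusion will be collected" and has five items. Its rhythm items are "New ventricular tachycardia, ventricular fibrillation or asystole" and "New cardiac arrhythmia requiring cardioversion". Its blood-pressure item covers vasopressor increases above a threshold and "Commencement of any vasopressor including norepinephrine, epinephrine, vasopressin, phenylephrine, and dopamine", so it looks only in the direction of hypotension. The other two items are hypoxaemia and a transfusion-type reaction. The second list runs to 24 hours and holds death, "Any cardiac arrest" and temperature.

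Appendix 3 lists acute hypertension and bradycardia with first-, second- or third-degree AV block among reactions to cryopreservatives such as DMSO. The responses it mentions are an ECG, atropine and pacing: "If bradycardia is present and ECG shows third degree atrio-ventricular block, consider placement of a temporary pacemaker". It says DMSO is added to all cryopreserved MSC products. Section 11 makes the cell product cryopreserved and the placebo Plasma-Lyte 148.

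Section 4.6 raises a theoretical concern that very high doses could activate the recipient's coagulation system. It adds "These effects have not been identified in patients treated with the dose range" of 1-3 million cells/kg. It gives the three phase 1 doses as "approx. 1.4, 2.8 and 5.7 million cells/kg for predicted body weight of 70kg", and the highest of these is the phase 2 dose.

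**The concern.** Pre-specified infusion events are collected in both arms whatever the investigator believes about cause. General AE reporting is not. Section 15.8 tells sites to leave out events that fit the underlying illness, unless the investigator links them to study drug or finds them unusually severe or frequent for that patient. An event on the list is therefore counted the same way at every site, and an event off the list depends on a judgement.

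The reactions left to that judgement include some that the protocol itself ties to a component present in one arm only. The primary focus of phase 2 is safety (sections 7 and 14.1). If a conduction or pressure reaction is recorded at one site and filtered out at another, the comparison between arms on that reaction is weakened. An analysis plan cannot recover events that were never collected.

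**Working it through.** **Step 1. Appendix 3 cryopreservative reactions against the 15.8 lists.**

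| Event | Meets a 15.8 item? |
|---|---|
| Asystole, cardiac arrest, death | Yes |
| Bradycardia with a vasopressor start, or an increase above the threshold | Yes, through the vasopressor item |
| Bradycardia or AV block managed with atropine or pacing, no vasopressor change | No: neither response is cardioversion |
| Bradycardia or AV block without treatment | No |
| Acute hypertension | No |

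Only the severe end of the conduction reactions is caught, and none of the hypertension.

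**Step 2. Who is exposed.** The cell product is cryopreserved and the placebo is not described as containing a cryopreservative. On the section 14.1 numbers, 30 patients per cohort are exposed in the cell arm and 0 in the placebo arm.

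**Step 3. Other routes of capture.**
- Vital signs (section 12.2, Day 1): heart rate and systolic and diastolic pressure before infusion, every 15 minutes during it, then hourly for 5 hours. This is free of attribution. It can show a slow rate or a high pressure, but rhythm is not among the recorded items.
- SAE reporting to day 90 (sections 15.7 and 15.8): a life-threatening block qualifies and enters the primary safety outcome.
- Non-serious AEs to day 90: subject to the filter above, applied by blinded investigators (section 10.3).

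**Step 4. What systematic collection could show.** The protocol gives no event rates, so those below are assumptions. With n = 30 cell-arm patients and every event collected, P(at least one) = 1 - (1 - p)^30:

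- p = 2%: 45%
- p = 5%: 79%
- p = 10%: 96%

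These chances hold only if no event is filtered out.

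**Step 5. Dose against the section 4.6 range.** The stated figures reproduce: 100/70 = 1.43, 200/70 = 2.86 (printed as 2.8) and 400/70 = 5.71 million cells/kg. Then 5.71/3 = 1.9, so at 70 kg the phase 2 dose is 1.9 times the top of the 1-3 million/kg range. The predicted weight at which 400 million cells would come down to 3 million/kg is 400/3 = 133 kg. The observation quoted in section 4.6 therefore does not extend to the phase 2 dose. Neither 15.8 list has a thrombotic item.

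**The case against.** The strongest reply is that a gap in one list is not a gap in the trial. The primary safety outcome is SAE incidence (section 7.1). Section 14.3 reports adverse events as well as the pre-specified ones. Heart rate and blood pressure are timed in everyone. Section 15.6 treats every serious adverse reaction as a SUSAR. Appendix 3 alerts staff to these very reactions, and a new AV block during an infusion is an unlikely candidate for dismissal as part of ARDS. The DMEC may also ask for any further data (section 3.3). Most of this stands. It narrows the gap without closing it: rhythm is not recorded with the vital signs, and a non-serious reaction still depends on site judgement. Blood-pressure events in ventilated patients are the likelier ones to be filtered out.

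On coagulation the reply is stronger. Section 4.6 speaks of a theoretical concern at very high doses, and of activation rather than clinical thrombosis. Section 12.3 measures a coagulation panel, and section 8.3 excludes recent or treated venous thromboembolism. Sections 4.5 and 4.6 cite a nine-patient trial of a different MSC product at 1, 5 and 10 million cells/kg, reported as safe. Against that, the translational samples are taken where possible, on day 0 and next on day 4 (Table 2), and daily coagulation results depend on standard care. This part is therefore secondary.

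The 6- and 24-hour windows suit infusion-associated events and are not an error.

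**Conclusion.** The mismatch between section 15.8 and Appendix 3 is a fact of the text and should be corrected. What lacks systematic, attribution-free collection is bradycardia or AV block short of asystole, arrest, death or a vasopressor change, together with acute hypertension. The exposure contrast is 30 against 0 patients per cohort. This assumes that the placebo contains no cryopreservative, as section 11 implies, and that Appendix 3 lists possible reactions; it forecasts no incidence. The thromboembolic part is a lower-priority addition.

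Three stronger readings are tempting and not supported:
- That cell-arm harm would go unseen. The SAE, AE and vital-sign routes and the severe-end items rule that out.
- That section 4.6 shows a thrombotic risk at the phase 2 dose. It shows only that the quoted observation covers a lower range.
- That 0 of 3 phase 1 patients at 400 million cells leaves a rate of up to 63% for these events. That bound (1 - 0.05^(1/3)) concerns dose-limiting toxicity, defined as any serious adverse reaction. It does not bear on whether the list is adequate.

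**What to change.** Reconcile section 15.8 with Appendix 3:

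1. Widen the third 6-hour item to any new arrhythmia, including bradycardia or AV block, that leads to drug treatment, pacing or cardioversion.
2. Add acute hypertension that leads to pausing of the infusion or to treatment.
3. State that both are collected in both arms regardless of attribution, and tabulated by arm beside the timed heart rate and blood pressure.

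As a second, lower priority, collect venous and arterial thromboembolic events in both arms. Exempt them from the underlying-condition filter, keep the existing day-90 limit, and include them in the DMEC report.

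These changes affect what is recorded, not dose or clinical management. The cost is protocol wording and a few CRF fields, with no new tests. The downside is more non-specific events recorded in both arms.
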